#### Follow-up

A full blood count will be performed at day 1 (24 h) after delivery to assess haemoglobin and haematocrit. Clinical follow-up of the mother will be completed before hospital discharge.

#### Outcome measures

The primary outcome measures are PPH (measured blood loss > 500 mL). Measured blood loss of ≥ 500 mL has been chosen as a clinically relevant outcome and to allow direct comparisons with other studies. It is widely accepted that clinicians underestimate rather than overestimate blood loss and for this study we will formally measure blood loss rather than relying on subjective estimates.

Secondary outcomes include the incidence of side effects following administration of oxytocin, mean estimated blood loss, major obstetric haemorrhage (measured loss ≥ 1000 mL), change in haemoglobin and haematocrit, significant anaemia (Hb fall ≥ 20%) 24 h after delivery, need for blood transfusion, length of postnatal stay in hospital (and specifically admission for high-dependency care) and the need for an additional uterotonic agent. Hypotension will be defined as a fall in blood pressure > 30% below the pre-delivery blood pressure and/or use of ephedrine and tachycardia will be defined as a persistent heart rate of above 100 bpm.

#### Definition of end-of-trial

The trial will be considered complete after the final review of the last trial participant. Trial completion will be notified to the Competent Authority and the Ethics Committees using the appropriate form.

#### Withdrawal of research participants from study protocol

Women who previously agreed to participate in the trial can voluntarily withdraw their consent and they are not obliged to give a reason for their withdrawal. This is written in the research participant’s information leaflet and will be explained during the consenting procedure.

Women will be withdrawn from the trial if their primary care giver has decided on the preferred route of oxytocin administration for the third stage.

The reason for withdrawal will be recorded in the CRF of the trial and the management for the women who are withdrawn from the trial will follow routine hospital care or as specified by the primary clinician caring for them.

#### Statistical analysis

Data analysis and reporting will proceed according to CONSORT guidelines [24] for RCTs and will be conducted blinded to group status by the trial statistician and researcher (Fig. 2). The first stage of analysis will be to use descriptive statistics to describe recruited individuals in relation to those eligible and to investigate comparability of the trial arms at baseline. The primary analyses will involve intention-to-treat comparisons between the two groups for the primary outcomes, with transformation as appropriate after examination of distributions and adjusted for stratification variables (i.e. parity). The study aims to evaluate haemorrhage at vaginal delivery and women who deliver by Caesarean section will be excluded post-randomisation and accounted for in the CONSORT diagram. Secondary analyses will investigate the effects of further adjustment for any variables displaying marked imbalance between the arms at baseline. Secondary outcomes will be analysed in a similar way. All analyses will use appropriate (that is, logistic or linear) regression models, with results presented as point estimates (odds ratios or difference in means), 95% confidence intervals and *p* values. Further secondary analyses will involve planned subgroup analyses and will use multivariable regression models with appropriate interaction terms to ascertain any differential effects in relation to induction of labour, parity and history of previous postpartum haemorrhage. The SPIRIT Checklist is provided as Additional file 1.

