#### Secondary outcomes

To compare the incidence of side effects following administration of oxytocin (headache, vomiting, hypotension, tachycardia);to compare the estimated mean blood loss and early lochial loss following IM oxytocin compared with IV oxytocin;to compare the incidence of major obstetric haemorrhage (measured blood loss ≥ 1000 mL);to compare the objective change in haemoglobin and haematocrit before and 24 h after delivery between the two groups;to compare the incidence of severe anaemia (Hb fall ≥ 20%) 24 h after delivery between the two groups (or patient transfused);to compare the need for blood transfusion and/or blood products;to compare the need for an additional uterotonic agent between the two groups;to compare the postnatal length of stay in labour ward/HDU and in the hospital.

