### Intervention

Women will be informed of the study antenatally in the outpatient clinics and antenatal classes; they will be provided with an information leaflet which has been approved by the Research Ethics Committee in National Maternity Hospital by the research fellow. Formal recruitment and written consent will take place when women attend the assessment unit with symptoms and signs of early labour or when they are admitted for induction. The admitting midwife will approach potentially eligible women and establish whether they are suitable for recruitment. A research fellow/midwife will approach eligible women and seek written informed consent (see ‘Screening procedure’). Following written informed consent, the chart will be labelled with a trial sticker in order to inform the participants’ carers, i.e. midwives and obstetricians, that she is participating in the study.

When the woman is confirmed to be in labour or is ready to have her labour induced, she will be brought into a room in the delivery suite. When a cannula is being sited (e.g. for epidural, IV fluid or syntocinon infusion, which is common practice) a sample will be taken for a full blood count at the same time. Randomised allocation will take place when the second stage of labour has been diagnosed in nulliparous women. For multiparous women, random allocation will take place when they have been diagnosed in active labour and vaginal delivery is considered imminent. Following randomisation, the woman will be allocated to receive either IM oxytocin 10 IU and a placebo (1 mL 0.9% normal saline) intravenously or IV oxytocin 10 IU slow bolus over 1 min and a placebo (1 mL 0.9% normal saline) intramuscularly.

The syntocinon and the normal saline ampoules to be used in the trial are currently being used routinely in the delivery suite in the Coombe Women & Infants University Hospital.

Name of the medicinal product: syntocinon 10 IU/mL solution for infusion or injection. Marketing authorisation holder: Sigma-Tau Industrie Farmaceutiche.

Name of placebo: sodium chloride 0.9% w/v injection BP. Marketing authorisation holder: Noridem Enterprises Ltd.

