#### Sample size

We estimate from the Coombe Hospital annual report in 2010 and a retrospective audit of labour ward deliveries that 6–10% of study participants will have an estimated blood loss of > 500 mL. These estimates are based on observed recording of haemorrhage and it is well recognised that obstetricians and midwives underestimate blood loss. It is therefore likely that the rate of postpartum haemorrhage based on measured blood loss will be higher, consistent with our findings on the ECSSIT trial [25].

With 500 patients per group for analysis, the study will have 80% power at the 5% two-sided alpha level, to detect differences in the proportion of patients with measured blood loss > 500 mL of 10% vs 5% or 15% vs 9%, equivalent to odds ratios of 0.50 and 0.55, respectively. It could be argued that any difference in effect on the primary clinical outcome would be worth detecting. Rather, given the need for timely delivery of evidence, we have specified detectable differences for realistic sample sizes recruited within a reasonable time frame within the constraints of the available funding. The results can be included in future Cochrane systematic reviews and may support funding of a future larger trial if smaller but clinically relevant differences are detected.

Over the course of 18 months we aim to recruit a minimum of 1000 patients representing 20% of the available population; this conservative estimate takes account of eligibility criteria and non-English speaking women. The final sample size will be slightly inflated to allow for women who subsequently deliver by Caesarean section and for missing outcome data (blood loss not measured or full blood count not taken at the correct time).

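### Change in haemoglobin and haematocrit is compared with adjustment for parity only, so the pre-delivery value already collected goes unused in the main model and some precision may be lost

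*Protocol article*

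**What the plan says.** All references are to the protocol article.

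- **Outcome.** Secondary outcomes lists the aim "to compare the objective change in haemoglobin and haematocrit before and 24 h after delivery between the two groups".
- **Measurements.** Under Intervention, when the cannula is sited, "a sample will be taken for a full blood count at the same time". Under Follow-up, "A full blood count will be performed at day 1 (24 h) after delivery to assess haemoglobin and haematocrit".
- **Main model.** Statistical analysis says the primary comparisons are by intention to treat and "adjusted for stratification variables (i.e. parity"). It then says "Secondary outcomes will be analysed in a similar way" and "All analyses will use appropriate (that is, logistic or linear) regression models", with differences in means for continuous outcomes.
- **Other adjustment.** The same section adds: "Secondary analyses will investigate the effects of further adjustment for any variables displaying marked imbalance between the arms at baseline".

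Pre-delivery haemoglobin or haematocrit is not named as a covariate anywhere. Randomisation is stratified by parity alone, so the design does not balance either measure.

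**The concern.** Subtracting the pre-delivery value is not the same as adjusting for it. A change score fixes the coefficient of the baseline value at one. When the regression slope of the 24 h value on the baseline value is below one, which is the usual pattern with equal SDs, subtraction over-corrects. Two things follow:

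- The treatment contrast carries avoidable noise.
- A chance difference between the arms in pre-delivery haemoglobin moves the contrast in the opposite direction, through regression to the mean.

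These blood counts matter because they give a check on haemorrhage that does not rest on weighing. The article concedes, in its account of blood-loss measurement, that estimates may differ with the duration of collection. It also uses different collection methods for normal and assisted deliveries. The laboratory comparison should therefore be as sharp as the collected data allow.

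**Working it through.** **The plan's own figures.** The article gives no effect size, SD, correlation or power for haemoglobin or haematocrit, so there is no figure to reproduce for this outcome. Its only power statement is 80% with 500 per group for the primary outcome. A pooled normal approximation gives 85.2% for 10% vs 5% and 83.2% for 15% vs 9%; with a continuity correction, 82.2% and 80.6%. The stated power is met, and it has no bearing on this point.

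**Inputs.** From the article: 500 women per group. Assumed: the correlation r between pre-delivery and 24 h values, and the ratio of their SDs.

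**Step 1: precision with equal SDs (s).**
- Variance of the change score: 2(1 − r)s².
- Residual variance after baseline adjustment: (1 − r²)s².
- Ratio, adjusted to change score: (1 − r²) / [2(1 − r)] = (1 + r)/2.
- Confidence-interval width is multiplied by the square root of this ratio.
- Women per arm a change-score analysis would need to match 500 per arm with adjustment: 500 / ratio.
- Power of the change score where the adjusted analysis has 80%: Φ[(1.96 + 0.84)√ratio − 1.96].

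| r | Variance ratio | CI narrower by | Equivalent n per arm | Change-score power when adjusted = 80% |
|---|---|---|---|---|
| 0.5 | 0.75 | 13% | 667 | 67.9% |
| 0.6 | 0.80 | 11% | 625 | 70.7% |
| 0.7 | 0.85 | 8% | 588 | 73.3% |
| 0.8 | 0.90 | 5% | 556 | 75.7% |

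**Step 2: unequal SDs.** Set the pre-delivery SD to 1 and the 24 h SD to 1.2 (assumed; variable blood loss could widen the later values). The change-score variance is 1 + 1.44 − 2.4r and the adjusted variance is 1.44(1 − r²).
- r = 0.5: 1.08 / 1.24 = 0.87, interval about 7% narrower.
- r = 0.7: 0.734 / 0.76 = 0.97, about 2% narrower.
- r = 0.8: 0.518 / 0.52 = 0.997, under 0.2% narrower.

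In general the change-score variance minus the adjusted variance equals (s_pre − r·s_post)². This cannot be negative, so in large samples adjustment never loses precision. It is zero only when the slope r·s_post/s_pre equals one.

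**Step 3: shift from a chance baseline difference, equal SDs.** With 500 per arm the difference in baseline means has standard error √(2/500) = 0.063 SD, so its 95% range is ±1.96 × 0.063 = ±0.124 SD. A baseline difference D moves the change-score contrast by −(1 − r)D. The contrast's standard error is √[2(1 − r)] × 0.063. For D = 0.124 SD:
- r = 0.5: shift 0.062 SD, or 0.98 standard errors.
- r = 0.7: shift 0.037 SD, or 0.76 standard errors.
- r = 0.8: shift 0.025 SD, or 0.62 standard errors.

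These are values at the edge of the 95% range; a typical imbalance would do less.

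**Step 4: is the covariate usable?** The first count is taken at cannulation, a step described before randomisation, and the trial injections are given only after the birth. The value therefore cannot be affected by treatment. Every woman whose change can be computed has it, so adding it loses nobody from the change analysis.

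**The case against.** **The parity clause is written for the primary outcomes.** Haemoglobin and haematocrit are reached only through the sentence on similar analysis, and similar is not identical. An SAP that is not shown might name outcome-specific covariates. This lowers certainty about what will be done. It does not remove the point, because the article states a closed adjustment set, carries it over, and gives another route only for imbalanced variables.

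**The marked-imbalance analysis already deals with the shift.** In part: it would act where the shift is largest. But it is secondary, has no threshold, depends on the observed data and leaves the main estimate as it is. It does not recover precision when baseline happens to be balanced.

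**The gain may be small.** This stands. It depends wholly on a correlation and an SD ratio that the article does not give, and Step 2 shows that it can nearly vanish.

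**Stronger readings that the article does not support.**
- A reader might infer that the planned comparison is biased or invalid. It is not. Randomisation makes the change-score contrast unbiased with valid confidence intervals; the shift is conditional on the imbalance seen in one trial.
- A reader might infer from "missing outcome data (blood loss not measured or full blood count not taken at the correct time") that off-time blood counts will be deleted from the analysis. That sentence, under Sample size, explains an allowance in recruitment and sets no analysis rule. Nor does it justify adding hours since birth as a covariate: that is a post-randomisation variable, possibly related to bleeding or discharge, and the article does not say that sampling times are recorded. It gives no basis for an imputation rule either.

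**Conclusion.** The point holds as a free improvement in efficiency, not as an error that invalidates a result. As written, the main comparison of change in haemoglobin and haematocrit leaves out a baseline value that the trial collects. Under equal SDs and r from 0.5 to 0.8, the variance could be cut to 0.75 to 0.90 of its planned size and the interval narrowed by 13% to 5%. With a larger 24 h SD the gain is smaller and can approach zero. Both r and the SD ratio are assumptions. That adjustment does not worsen the large-sample variance holds whatever their values. The consequence is confined to these secondary outcomes.

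**What to change.** Add one sentence to Statistical analysis: haemoglobin and haematocrit will each be analysed by linear regression of the 24 h value on arm, parity and the woman's own pre-delivery value of the same measure, in the main analysis and whatever the observed balance. The change may be kept as the dependent variable if preferred. With the pre-delivery value in the model, the arm coefficient is identical, because only the baseline coefficient changes (by one).

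The cost is that sentence. It needs no new measurement and no extra women. The article describes the trial as ongoing, so the wording can be settled before the data are analysed.

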#### Method of assigning treatment groups

##### Randomisation

Randomisation will be performed using an automated web-based randomisation system hosted by the Nottingham Clinical Trials Unit, a UKCRC-registered trials unit thereby ensuring concealment. Allocation will be stratified by parity (nulliparous/multiparous), and blocked using random permuted blocks of varying size.

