#### Standard arm: intramuscular oxytocin and placebo

##### Uterotonic agent

Immediately following delivery of the baby and preferably within 1 min of birth, oxytocin 10 IU is given intramuscularly into the thigh muscle and 1 mL 0.9% normal saline is given intravenously through the cannula.

The steps involving umbilical cord clamping and placental delivery are the same as in the experimental arm.

The two interventions only differ in the route of administering oxytocin and the placebo.

Blood loss following vaginal deliveries will be measured by direct collection of blood and the gravimetric method.

For women who have a normal vaginal delivery, a fresh delivery sheet is placed under her buttocks as soon as the baby is born and placed on the woman’s chest/abdomen. Once there is no concern of further active bleeding, the blood loss will be estimated by weighing all the soiled materials (swabs, pads, disposable sheets) on a scale and subtracting the known weights of these materials to determine the blood loss. Women remain on the labour ward for a minimum of 1 h after the birth and are monitored throughout that time period. They are then transferred to the postnatal ward if there are no apparent complications.

For women who have an assisted vaginal delivery, Comfy Guard®, a surgical drape with a pouch for collecting vaginal blood loss, will be placed under the woman’s buttocks in preparation for birth and before delivery of the placenta. The bag is transparent allowing continuous monitoring of blood loss. The bag will be left in situ until the birth attendant is no longer concerned about blood loss, such as when a sanitary towel is applied to the vulva. The blood collected in the surgical drape will be weighed. Blood-soaked swabs and additional drapes will also be weighed and the known dry weight of the swabs and drapes will be subtracted. This volume will be added to the measured blood volume from the surgical drape.

Any delayed blood loss occurring within 24 h of delivery will also be recorded. It is possible that there may be a difference in estimates of blood loss based on different durations of blood loss collection for women with early or delayed transfer to the postnatal ward. This potential limitation will be addressed by routinely documenting any additional significant blood loss within 24 h of delivery.

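### Covariates for the further-adjusted secondary analyses are selected by observed baseline imbalance rather than by expected relation to blood loss

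*Protocol article*

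**What the plan says.** All of the following is in the protocol article.

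- **Primary analysis** (Statistical analysis): an intention-to-treat comparison with parity as the only named covariate ("adjusted for stratification variables (i.e. parity"). This matches the design (Randomisation): "Allocation will be stratified by parity (nulliparous/multiparous), and blocked using random permuted blocks of varying size". The randomisation system is web-based, with concealment.
- **First stage of analysis** (Statistical analysis): descriptive statistics are used, among other things, "to investigate comparability of the trial arms at baseline".
- **Further adjustment** (Statistical analysis): "Secondary analyses will investigate the effects of further adjustment for any variables displaying marked imbalance between the arms at baseline". Secondary outcomes are to be handled similarly.
- **Models** (Statistical analysis): "All analyses will use appropriate (that is, logistic or linear) regression models".
- **Subgroups** (Statistical analysis): interaction terms are planned "to ascertain any differential effects in relation to induction of labour, parity and history of previous postpartum haemorrhage". Induction and previous haemorrhage are named only here, not as covariates.
- **Blinding of the analysis** (Statistical analysis): it "will be conducted blinded to group status by the trial statistician and researcher".
- **Measurement of blood loss** (Standard arm, Uterotonic agent): after normal birth, soiled materials are weighed. A different method, a collecting drape plus weighed swabs, applies "For women who have an assisted vaginal delivery".

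**The concern.** Bias from a chance imbalance is roughly the imbalance multiplied by the strength of the variable's relation to the outcome. The stated rule looks only at the first factor. An uneven variable with no relation to blood loss enters the model. A strong predictor with a moderate imbalance stays out. A strong predictor that is well balanced also stays out, although adjusting for it would still add power.

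At stake is how useful the further-adjusted estimates are, for the primary and the secondary outcomes. Their covariate set is settled only after the baseline comparison has been seen, and it need not contain the variables that would make the adjustment worthwhile. This is not a detail deferred to an analysis plan: the article states the criterion, and the criterion is the problem.

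**Working it through.** **1. The plan's own figure.** The article gives no number for this rule. Its nearest figure is 80% power with 500 per group at two-sided 5% (Sample size). With power = Φ[(d − 1.96·SE₀)/SE₁], where SE₀ is pooled and SE₁ unpooled:

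- 10% vs 5%: SE₀ = √(2 × 0.075 × 0.925/500) = 0.01666 and SE₁ = √((0.09 + 0.0475)/500) = 0.01658. Power is 85.2%, or 82.3% with continuity correction.
- 15% vs 9%: 83.2%, or 80.7% with continuity correction.
- 10% with the stated odds ratio of 0.50 (5.26% in the other arm): 80.6%.

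The 80% is reproduced within the usual variants, and nothing below changes it.

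**2. How often chance alone triggers the rule.** For k independent baseline variables, each flagged with probability a, P(at least one flagged) = 1 − (1 − a)^k. The article gives no cut, so a range is needed.

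- Assumed 5% test: k = 5 gives 22.6%, k = 10 gives 40.1%, k = 15 gives 53.7%, k = 20 gives 64%.
- Assumed standardised-difference cut, k = 20: the SE is √(2/500) = 0.063. A cut of 0.2 SD (z = 3.16) gives about 3%. A cut of 0.1 SD (z = 1.58) gives about 91%.

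The trigger rate therefore runs from about 3% to 91%. It shows that chance can trigger the rule, but it is not a measure of harm.

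**3. What an unflagged predictor can do.** Assume a binary factor present in 25% of women, with haemorrhage risks of 20% (factor present) and 8% (absent). None of these figures is in the article.

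- SE of the difference in prevalence = √(2 × 0.25 × 0.75/500) = 0.0274. A 4-point imbalance has z = 0.04/0.0274 = 1.46, which a 5% test does not flag.
- Shift in the haemorrhage difference = 0.04 × (0.20 − 0.08) = 0.0048, or 0.48 points. This is about 10% of the 5-point target.
- Just under z = 1.96: 1.96 × 0.0274 × 0.12 = 0.0064, or 0.64 points (about 13%).
- Halving or doubling the 12-point risk gap turns 0.48 into 0.24 or 0.96 points.
- Against the sampling error: 0.48/1.66 = 0.29 standard errors.

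**4. Effect on power and type I error.** Both simulations used ten covariates, two of them prognostic. All settings are assumptions.

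| | Parity only | Parity + imbalance-selected | Parity + fixed prognostic set |
|---|---|---|---|
| A: power, OR 0.56, 500 per arm | 71.9% | 72.0% | 72.9% |
| B: power, conditional OR 0.50, prognostic OR 2 per SD, marked = abs(z) > 1.96 | 69.7% | 69.7% | 72.6% |
| B: type I error | 5.0% | 4.9% | 5.3% |

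Type I error in A was 5.3% to 5.5% for all three models. With 3,000 trials, each power figure has a Monte Carlo standard error of about √(0.7 × 0.3/3000) = 0.8 points, so the 1-point gain in A is only roughly determined. B's type I error used 6,000 null trials (standard error about 0.3 points). The absolute powers depend on the assumed settings and should not be set against the protocol's 80%.

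In B the rule flagged at least one variable in 40% of trials, and in more than 99% it left out at least one of the two prognostic covariates. That agrees with theory: both are flagged with probability 0.05² = 0.25%.

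**The case against.** The strongest reply is that little depends on these analyses. They are secondary, no conclusion is tied to them, and the primary model is fixed. Selection uses baseline data, and the analysts are blinded to group status. The 0.48-point shift is about 0.3 of a standard error, and the confidence interval already allows for chance imbalance of that kind. All of this stands and limits the weight. Blinding does not rescue the criterion, however: to see an imbalance the analyst must compare the arms at least as coded groups, and the comparison still says nothing about prognosis.

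A reader might infer more than the article supports:

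- **That the primary result is data-driven or its error rate inflated.** It is not: parity adjustment is fixed in advance, and neither simulation shows meaningful inflation.
- **That the rule has a 40% to 64% chance of a false flag.** That needs a 5% test. The article mentions only descriptive statistics, and other plausible cuts give about 3% to 91%.
- **That leaving marked undefined is itself an error.** A cut-off can be left to the analysis plan, which is not shown.
- **That the further-adjusted result is the designated robustness check on the primary endpoint.** The article does not give it that role.
- **That mode of birth belongs in the fixed baseline set.** Randomisation takes place at diagnosis of second stage in nulliparous women, or when birth is imminent in multiparous women (Intervention), before mode of birth is settled. The injections follow delivery, so treatment cannot plausibly affect it. That argument relies on intact blinding, and the research fellow who prepares the syringes is not blinded (Blinding). It is a post-randomisation, pre-treatment covariate and should be declared as one.

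**Conclusion.** The concern holds for the secondary further-adjusted analyses only. Their stated selection criterion is observed imbalance, which concealed randomisation makes a matter of chance. The covariate set therefore depends on the data, and under the simulated settings the adjustment gains essentially no power over parity alone.

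A set fixed for prognostic value would gain about 1 to 3 power points. That figure rests on two assumed prognostic covariates, with a stated strength only in simulation B (odds ratio 2 per SD). Weaker predictors would give less and stronger ones more. The larger benefit is that the adjusted model is settled independently of the observed imbalance. Weight: minor to moderate, with no effect on sample size, conduct or the primary conclusion.

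**What to change.** Replace the sentence with: *A secondary analysis will adjust for parity and induction of labour, plus any other baseline covariates named before unblinding for their expected relation to blood loss; observed imbalance will not add or drop covariates, and any adjustment prompted by it will be labelled post hoc.*

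The names should be on record before baseline data are compared even by coded arm, since blinding alone does not hide an imbalance. Induction is proposed because the article already singles it out as a subgroup factor. The article does not state that it predicts blood loss, so the investigators should confirm this.

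Optionally, add a separate sensitivity analysis that also includes spontaneous versus assisted birth, because it determines how blood loss is measured. State that this variable is known only after randomisation but before the blinded injection.

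The cost is one or two sentences. Induction is already needed for the planned subgroup analysis, and mode of birth is known from the delivery record and the measurement method. The downside is losing the freedom to react to a surprising imbalance within the planned analysis. Such an imbalance can still be described and explored as post hoc.
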